**Table 1 Tab1:**
[figure not shown]
Schedule of enrolment, interventions, and assessments

### Sample size

The power calculation is based on the main outcome, theoretical learning on short term. For the sample size determination, we considered 12 available seats for participants in each course. To achieve statistical power, we aimed for 8 clusters in both online and onsite arms (in total 16 clusters) to detect an increase in learning outcome of 20% (learning outcome increase of 5 points). We considered an intraclass correlation coefficient of 0.02, a standard deviation of 10, a power of 80%, and a two-sided alpha level of 5%. The Allocation Ratio was set at 1, implying an equal number of subjects in both online and onsite group.

Considering a dropout up to 2 students per course, equivalent to 17%, we determined that a total of 112 participants would be needed. This calculation factored in 10 clusters of 12 participants per study arm, which we deemed sufficient to assess any changes in learning outcome.

The sample size was estimated using the function n4means from the R package CRTSize [25].

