### Primary outcome

The primary outcome is short term learning (Kirkpatrick level 2).

Learning is assessed by a Multiple-Choice Questionnaire (MCQ) developed prior to the RCT specifically for this setting (Appendix 4). First the lecturers of the two courses were contacted and asked to provide five multiple choice questions presented as a stem with three answer options; one correct answer and two distractors. The questions should be related to core elements of their teaching under the heading of research training. The questions were set up to test the cognition of the students at the levels of "Knows" or "Knows how" according to Miller's Pyramid of Competence and not their behaviour [21]. Six of the course lecturers responded and out of this material all the questions which covered curriculum of both courses were selected. It was tested on 10 PhD students and within the lecturer group, revised after an item analysis and English language revised. The MCQ ended up containing 25 questions. The MCQ is filled in at baseline and repeated at the end of the course. The primary outcomes based on the MCQ is estimated as the score of learning calculated as number of correct answers out of 25 after the course. A decrease of points of the MCQ in the intervention groups denotes a deterioration of learning. In the MCQ the minimum score is 0 and 25 is maximum, where 19 indicates passing the course.

Furthermore, as secondary outcome, this outcome measurement will be categorized as binary outcome to determine passed/failed of the course defined by 75% (19/25) correct answers.

The learning score will be computed on group and individual level and compared regarding continued outcomes by the Mann–Whitney test comparing the learning score of the online and onsite groups. Regarding the binomial outcome of learning (passed/failed) data will be analysed by the Fisher’s exact test on an intention-to-treat basis between the online and onsite. The results will be presented as median and range and as mean and standard deviations, for possible future use in meta-analyses.

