### Limitations, generalizability, bias and strengths

It is a limitation to this study, that an onsite curriculum for a full day is delivered identically online, as this may favour the onsite course due to screen fatigue [33]. At the same time, it is also a strength that the time schedules are similar in both settings. The offer of coffee, tea, water, and a plain sandwich in the onsite course may better facilitate the possibility for socializing. Another limitation is that the study is performed in Denmark within a specific educational culture, with institutional policies and resources which might affect the outcome and limit generalization to other geographical settings. However, international students are welcome in the class.

In educational interventions it is generally difficult to blind participants and this inherent limitation also applies to this trial [11]. Thus, the participants are not blinded to their assigned intervention, and neither are the lecturers in the courses. However, the external statistical expert will be blinded when doing the analyses.

We chose to compare in-person onsite setting with a synchronous online setting. Therefore, the online setting cannot be expected to generalize to asynchronous online setting. Asynchronous delivery has in some cases showed positive results and it might be because students could go back and forth through the modules in the interface without time limit [11].

We will report on all the outcomes defined prior to conducting the study to avoid selective reporting bias.

It is a strength of the study that it seeks to report outcomes within the 1, 2 and 4 levels of the Kirkpatrick conceptual framework, and not solely on level 1. It is also a strength that the study is cluster randomized which will reduce “infections” between the two settings and has an adequate power calculated sample size and looks for a relevant educational difference of 20% between the online and onsite setting.

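### The planning SD of 10 points is not credible for a 0–25 score; the error is conservative, but the stated 80% power for 5 points does not describe this design

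*Protocol article*

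**What the plan says.** The Sample size section powers the trial on short-term learning and aims "to detect an increase in learning outcome of 20% (learning outcome increase of 5 points"). Its other inputs are: "We considered an intraclass correlation coefficient of 0.02, a standard deviation of 10, a power of 80%, and a two-sided alpha level of 5"%. For cluster size, "we considered 12 available seats for participants in each course". From these it derives 8 courses per arm, raised to 10 per arm to allow for up to 2 dropouts per course. It gives no source for the SD.

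The Primary outcome section defines the outcome as the post-course number of correct answers to 25 questions with three options each: "In the MCQ the minimum score is 0 and 25 is maximum, where 19 indicates passing the course".

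The section on limitations, generalizability, bias and strengths counts the power calculation as a strength and says that the study "looks for a relevant educational difference of 20% between the online and onsite setting".

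**The concern.** The SD and the scale do not fit together. On a score that runs only from 0 to 25, an SD of 10 describes students clustered near the two ends. That is not a plausible result for PhD students answering questions drawn from core elements of the teaching, directly after the course.

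The SD fixes both the stated power and the difference that the trial can detect. If it is much too large, the trial has far more than 80% power for 5 points and will also detect much smaller differences. A reader who takes the power statement at face value may then assume that a significant result points to a difference of about 5 points, and nothing in the design supports that assumption.

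**Working it through.** **Inputs.** From Sample size: difference 5 points, SD 10, ICC 0.02, 12 per course, 80% power, two-sided 5%, up to 2 dropouts per course (so 10 completers), 10 courses per arm planned. From Primary outcome: range 0 to 25, pass mark 19. Assumed here, because the article gives no observed SD: a realistic SD of 2.5 to 5 points, and ICC 0.10 as a less favourable alternative.

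**Step 1: reproduce the plan's figure.** The design effect is 1 + (12 − 1) × 0.02 = 1.22.
- With normal quantiles, n per arm = 2 × [10 × (1.960 + 0.842)/5]² × 1.22 = 62.8 × 1.22 = 76.6. That is 6.4 courses, rounded up to 7.
- With t quantiles on 2(k − 1) degrees of freedom, iterated, the result is 7.47 courses, rounded up to 8. This is the stated figure.

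The 10 was therefore entered in points, on the same scale as the 5. Had it been entered as 10% of the scale (2.5 points), the normal formula would give 76.6/16 = 4.8 students per arm, less than one course.

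**Step 2: how large can the SD be?** For a score bounded by 0 and 25 with mean μ, the SD cannot exceed √[μ(25 − μ)]. That limit is reached only if every student scores 0 or 25.

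| Mean | Largest possible SD |
|---|---|
| 12.5 | 12.5 |
| 19 | √(19 × 6) = 10.7 |
| 20 | √(20 × 5) = 10.0 |
| 21 | √(21 × 4) = 9.2 |
| 22 | √(22 × 3) = 8.1 |

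Scores spread evenly over 0 to 25 have SD √[(26² − 1)/12] = 7.5. There is a further consequence. If both arms have SD 10, neither mean can exceed 20. If the means also differ by 5, the lower is at most 15, which is 4 points below the pass mark.

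**Step 3: power and detectable difference for the planned design.** With 10 courses per arm and 10 completers each:
- Design effect at ICC 0.02: 1 + 9 × 0.02 = 1.18. At ICC 0.10: 1.90.
- Standard error of the mean difference = SD × √(2 × design effect/100), which is SD × 0.1536 at ICC 0.02 and SD × 0.1949 at ICC 0.10.
- Power comes from the noncentral t with 18 degrees of freedom.
- Difference detectable with 80% power ≈ (2.101 + 0.862) × standard error.

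| SD | Power for 5 points, ICC 0.02 | Detectable difference, ICC 0.02 | Detectable difference, ICC 0.10 |
|---|---|---|---|
| 10 (as planned) | 87% | 4.55 | 5.78 |
| 7.5 (even spread) | 98% | 3.41 | 4.33 |
| 5 (assumed) | >99.9% | 2.28 | 2.89 |
| 4 (assumed) | >99.9% | 1.82 | 2.31 |
| 3 (assumed) | >99.9% | 1.37 | 1.73 |
| 2.5 (assumed) | >99.9% | 1.14 | 1.44 |

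At ICC 0.10, power for 5 points is still 99.8% at SD 5. On the 25-point scale, 1.14 to 2.28 points is 4.6% to 9.1%, against the 20% in the power statement.

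**The case against.** **The calculation is right and the error is on the safe side.** Both parts stand. The inputs give 8 courses per arm, and a smaller SD raises power for 5 points. A reader might infer that the trial is underpowered or that the formula was misapplied. On this point neither is so, and the description of the sample size as adequate for 5 points survives.

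**Whether 5 points is educationally relevant does not depend on the SD.** That also stands. The target is 5/25 = 20% whatever the spread. What fails is the link between that target and the power of this design.

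**Any trial can find significance below its target difference.** True: with the plan's own SD of 10, an observed difference of about 2.101 × 1.536 = 3.2 points would already be significant. A realistic SD does not create that gap but widens it a good deal: at SD 4 the threshold falls to 2.101 × 0.614 = 1.3 points.

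**Misreporting is conjecture.** A reader might infer that the article will call any significant result relevant, or that it will report only a p-value. It says neither. The Primary outcome section promises medians with ranges and means with standard deviations, so the size of any difference will be visible.

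**The cause is unknown.** A reader might suspect that a 10% SD was combined with a difference in points. Nothing in the article confirms or excludes this.

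**How extreme SD 10 looks depends on the mean.** It is 80% of the absolute limit (10/12.5) and 94% of the limit at a mean of 19 (10/10.7). The article gives 19 as the pass mark, not as the expected mean. This softens the wording but does not rescue the figure: even an even spread over the whole scale gives only 7.5.

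**Conclusion.** The point holds as a wrong planning input. An SD of 10 is not credible for the post-course score as the article defines it, so 80% power for 5 points is not a description of this trial. The limits on the SD are mathematical and need no outside data.

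The size of the consequence rests on assumptions: SD 2.5 to 5, ICC 0.02 or 0.10, 10 completers in each of 10 courses per arm, and a comparison of means that allows for clustering. The article itself names a Mann–Whitney test, so the figures in points describe what the design can do and are not exact power values for that test. The main conclusion does not need the assumed range, since an SD of 7.5 already gives about 98% power at ICC 0.02.

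The practical result is limited. The trial is not short of power for its target because of this SD, and recruitment is unaffected. But a significant difference may be well under half of 5 points, so significance alone should not be read as the relevant difference.

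**What to change.** 1. Replace SD 10 with a justified SD for the final 25-item questionnaire, computed without reference to arm. The pooled post-course SD fits the outcome best. If arm labels are not used at all, a true arm difference d adds about d²/4 to the variance with equal arms, so the value errs high. Baseline scores could serve if the text says that they are pre-course. Two other sources fit less well: the test on 10 PhD students came before the questionnaire was revised and is very small, and the article does not say that the 2021 pilot used this questionnaire.
2. Restate, for 20 courses, the power for 5 points and the difference detectable with 80% power, with the ICC used.
3. Report the between-arm mean difference in the learning score with a 95% CI that allows for clustering by course, so that its size can be read against 5 points.

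Do not add an equivalence rule. The trial tests for a difference, and a margin of 5 points could label a sizeable gap as irrelevant: at SD 4, ICC 0.02, the CI half-width is about 1.3 points, so an observed gap of 3.7 points would lie within it. Leave the number of courses unchanged.

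The cost is one SD computation, a few restated figures and one added estimate with its interval. Recruitment and data collection do not change.

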**Methods:**

Cluster randomized trial with two parallel groups. Two PhD research training courses at the University of Copenhagen are randomized to online (Zoom) or onsite (The Parker Institute, Denmark) setting. Enrolled students are invited to participate in the study. Primary outcome is short term learning. Secondary outcomes are short term preference, motivation, self-efficacy, and long-term academic achievements. Standardized, reproducible and feasible outcomes will be measured by tailor made multiple choice questionnaires, evaluation survey, frequently used Intrinsic Motivation Inventory, Single Item Self-Efficacy Question, and Google Scholar publication data. Sample size is calculated to 20 clusters and courses are randomized by a computer random number generator. Statistical analyses will be performed blinded by an external statistical expert.

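### The stated requirement of 112 participants in total contradicts the protocol's own cluster counts; it matches one arm, and as a true total it falls well short of 80% power

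*Protocol article*

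**What the plan says.** The Sample size section takes 12 seats per course, a difference of 5 points on the 25-item test, an SD of 10, an intraclass correlation of 0.02, 80% power, a two-sided 5% level and equal allocation. From these it arrives at 8 clusters per arm, 16 in all. It then allows for up to 2 dropouts per course, equated to 17%, and concludes that "we determined that a total of 112 participants would be needed". The next sentence reads: "This calculation factored in 10 clusters of 12 participants per study arm". The calculation is attributed to the n4means function of the R package CRTSize.

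Elsewhere the size is given in courses only. The Abstract (Methods) states: "Sample size is calculated to 20 clusters". The Recruitment section plans 10 runs of each of the two courses, so 20 in all.

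**The concern.** An allowance for dropout can only raise the number required. Here the section moves from 16 courses of 12 (192 students before dropout) to 112 after dropout, and then to 20 courses of 12 (240). The stated total is smaller than a single arm of the design it is said to describe.

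The required sample size is the number against which recruitment is judged, and 112 is the only participant total in the document. If it is read literally, the trial could be stopped, or reported as fully recruited, at about half the size its own assumptions require. Under-filled courses are foreseeable: consent is voluntary, and the Trial design section expects course sizes to differ. The Discussion also claims an adequately powered sample size as a strength. That would not be true of 112 students in total.

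**Working it through.** **Inputs (all from the Sample size section).** Difference d = 5; SD s = 10; intraclass correlation ρ = 0.02; seats per course m = 12; two-sided α = 0.05; power 0.80; 1:1 allocation; dropout 2 of 12.

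**Step 1. Reproduce the number of clusters.** Design effect = 1 + (m − 1)ρ = 1 + 11 × 0.02 = 1.22. Clusters per arm:

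k = 2 s² (q₁ + q₂)² × 1.22 / (m d²)

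- With normal quantiles: 2 × 100 × (1.960 + 0.842)² × 1.22 / (12 × 25) = 6.4.
- With t quantiles on 2(k − 1) degrees of freedom, iterated: 7.47, rounded up to **8**.

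The protocol's 8 clusters per arm is therefore reproduced.

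**Step 2. Try to reproduce 112.**

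- One arm: 8 × 12 = 96, and 96 × (1 + 2/12) = **112.0** exactly.
- 112 / 12 = 9.33 courses, rounded up to 10, which is the number of courses per arm in the next sentence.
- Both arms: 192 × 7/6 = 224.
- Inflating by division: 96 / (10/12) = 115.2, so 116 per arm and about 231 in total.
- Totals before any dropout: 126 with no clustering, 154 with the design effect and normal quantiles, 192 with 8 × 12 per arm.

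No route from the stated inputs gives 112 as a total. Even with individual randomisation and no dropout, 112 in total gives only 75.4% power.

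**Step 3. Power at different sizes.** With k courses per arm and m students per course, the standard error is s√(2[1 + (m − 1)ρ]/(km)) and the non-centrality is λ = d / SE. The t version uses the non-central t with 2(k − 1) degrees of freedom.

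| Scenario | k per arm | m | λ | Power, t | Power, normal |
|---|---|---|---|---|---|
| 112 in total, full courses | 4.67 | 12 | 2.40 | 54.7% | 66.8% |
| Same, after 17% dropout | 4.67 | 10 | 2.22 | 48.9% | 60.4% |
| 112 in total, spread over 20 courses | 10 | 5.6 | 2.53 | 66.8% | 71.6% |
| Same, after 17% dropout | 10 | 4.67 | 2.33 | 59.7% | 64.5% |
| 8 courses per arm, no dropout | 8 | 12 | 3.14 | 83.0% | 88.0% |
| 8 courses per arm, 10 completers each | 8 | 10 | 2.91 | 77.2% | 82.9% |
| 10 courses per arm, 10 completers each | 10 | 10 | 3.25 | 86.8% | 90.2% |

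The t version suits so few clusters, and it is the version that reproduces the protocol's 8 per arm.

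**The case against.** The strongest reply is that nothing operational depends on 112. It appears once. Every other statement of size is in courses: 20 clusters in the Abstract, 10 per arm in the Sample size section, 10 runs of each course under Recruitment. Randomisation is by course, and the primary analysis waits for the last included course. No stopping rule refers to 112 participants, and the planned trial exceeds 80% power. This is correct. It means that the plan is not undersized, that the harm depends on how the figure is used, and that the correction costs little. It does not make the figure right, and a later report would quite naturally quote it as the target.

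Three narrower points also have weight:

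- The per-arm origin is an inference, because the protocol does not state it. It is an exact match, but the contradiction holds whatever the origin.
- The power figures for 112 in total describe hypothetical trials and vary with how students are spread and with the approximation used. Since 112 is said to allow for dropout already, the matching t-based range is 49% to 60%; the 67% end assumes no dropout. No variant reaches 80%.
- Multiplying by 1.17 instead of dividing by 0.83 makes no practical difference here. Both 112 and 116 per arm round up to 10 courses of 12.

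**Conclusion.** The statement is wrong as written. A total of 112 is incompatible with the 192 students implied before dropout and with the 240 in the design as described, and it is almost certainly the inflated size of one arm. The corresponding total is 224 by the protocol's apparent method, or about 231 if the inflation is done by division. A true total of 112 would give about 49% to 67% power on a t basis instead of 80%, depending on dropout and on how students are spread over courses.

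These powers rest on the protocol's own difference, SD and intraclass correlation, on equal course sizes, and on a comparison of means that allows for clustering. The error is confined to the participant total: the 8 clusters per arm reproduce, and the planned 20 courses have about 87% power with 10 completers each.

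**What to change.** Replace the sentence giving the total, for example with: *Ten courses of 12 seats per arm (20 courses, 240 students enrolled, 200 expected to complete after up to 2 dropouts per course) give about 87% power under the stated assumptions; 8 courses of 12 per arm (192 students) is the minimum without dropout.*

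Add that completion of recruitment is defined by 20 courses and not by a count of 112 participants. Before the power figure is printed, the sponsor should confirm it from its own n4means run and state that it assumes a cluster-adjusted comparison of means with equal course sizes; the normal approximation would give about 90%. If the inflation is shown, it should divide by the completion proportion.

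The cost is one corrected sentence here and wherever the figure is repeated. No recruitment is added, because 20 courses are already planned.

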### Recruitment

Participants are PhD students enrolled in 10 courses of “Practical Course in Systematic Review Technique in Clinical Research” and 10 courses of “Getting started: Writing your first manuscript for publication” at the PhD School of the Faculty of Health Sciences, University of Copenhagen, Denmark.

### Assignment of interventions: allocation

Randomization will be performed on course-level. The courses are randomized by a computer random number generator [26]. To get a balanced randomization per year, 2 sets with 2 unique random integers in each, taken from the 1–4 range is requested.

The setting is not included in the course catalogue of the PhD School and thus allocation to online or onsite is concealed until 3–4 weeks before course commencement when a welcome letter with course information including allocation to online or onsite setting is distributed to the students. The lecturers are also informed of the course setting at this time point. If students withdraw from the course after being informed of the setting, a letter is sent to them enquiring of the reason for withdrawal and reason is recorded (Appendix 7).

The allocation sequence is generated by a computer random number generator (random.org). The participants and the lecturers sign up for the course without knowing the course setting (online or onsite) until 3–4 weeks before the course.

### Assignment of interventions: blinding

Due to the nature of the study, it is not possible to blind trial participants or lecturers. The outcomes are reported by the participants directly in an online form, thus being blinded for the outcome assessor, but not for the individual participant. The data collection for the long-term follow-up regarding academic achievements is conducted without blinding. However, the external researcher analysing the data will be blinded.

### Data collection and management

Data will be collected by the project leader (Table 1). Baseline variables and post course knowledge, motivation, and self-efficacy are self-reported through questionnaires in SurveyXact® [27]. Academic achievements are collected through Google Scholar profiles of the participants.

Given that we are using participant assessments and evaluations for research purposes, all data collection – except for monthly follow-up of academic achievements after the course – takes place either in the immediate beginning or ending of the course and therefore we expect participant retention to be high.

Data will be downloaded from SurveyXact and stored in a locked and logged drive on a computer belonging to the Capital Region of Denmark. Only the project leader has access to the data.

This project conduct is following the Danish Data Protection Agency guidelines of the European GDPR throughout the trial. Following the end of the trial, data will be stored at the Danish National Data Archive which fulfil Danish and European guidelines for data protection and management.

